### Randomization

Before the study begins, permuted-block randomization will be generated for 85 patients by a statistician using SAS computer software (SAS Institute) and block sizes of 3, an allocation ratio of 1:1:1, and one strata to minimize the imbalance in the number allocated to each group. Then, the randomization schedule will be transcribed in sequentially numbered and opaque sealed envelopes by a research coordinator not involved in assignment allocation to ensure allocation concealment. The allocation list will be stored in a locked filing cabinet of the principal investigator and will not made accessible to the interventionist involved in enrollment and treatment allocation.

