## Methods

### Trial Design

This research study is designed as a randomized, controlled, patient-blinded, single-center superiority trial with 3 parallel groups and a 1:1:1 allocation ratio. A modified Consolidated Standards of Reporting Trials flow diagram for individual RCTs of nonpharmacologic treatments will be used to document recruitment and retention of participants (see Multimedia Appendix 1) [43].

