### Participants

This RCT targets adults admitted to the ICU after undergoing cardiac surgery in a university-affiliated hospital in Canada. A single setting was selected for this study because of standardized pain management practices and surgical techniques and single patient rooms. Patients will be screened for inclusion using the eligibility criteria seen in Textbox 1. Patients at higher risk of postoperative complications and those with contradictions to having their hands massaged will be excluded.

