### Recruitment of Participants

Patient recruitment will begin preoperatively when eligibility criteria such as age and language spoken will be verified (Table 1).

The remaining eligibility criteria (eg, blood loss, peripheral intravenous lines) will be evaluated post–cardiac surgery and ICU admission. After the collection of baseline data, patients meeting all the inclusion criteria will be randomly assigned to either hand massage, hand-holding, or standard care. As each participant enters the study, he or she receives the next envelope in the sequence, thereby concealing the interventionist’s and trial participants’ knowledge of the upcoming group assignment.

The interventionist will then administer the assigned intervention (hand massage, hand-holding) without informing participants of their group assignment until the end of data collection. Nurses and other ICU clinicians will also be masked to patients’ group assignment. The similarity of the hand massage and hand-holding therapy characteristics serves to mask study participants and clinicians with regard to the specific intervention received as observed in a feasibility and acceptability study where patients receiving hand-holding referred to the intervention as massage [42]. Conversely, patients in the rest group are less likely to be masked to the group assigned.

A modified Consolidated Standards of Reporting Trials flow diagram for individual RCTs of nonpharmacologic treatments will be used to document recruitment and retention of participants [43].

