### Interventions

#### Training of Interventionist and Timing of Interventions

Eligible patients will be randomized in equal proportions between hand massage, hand-holding, and standard care. One interventionist will deliver the hand massage and hand-holding interventions, which will be standardized across participants. The interventionist is a registered nurse with no previous experience in massage therapy who will be trained by a professional massage therapist through an accredited workshop of 6 hours including practical exercises and verification of competency, as was done in the pilot RCT [30].

The first intervention (hand massage or hand-holding) will be delivered in the evening of the day of surgery and the remaining two interventions the day after when patients are still in the ICU. Overall, three interventions will be administered within 24 hours postoperatively over the course of two days.

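### With fixed blocks of 3 for three arms and one interventionist who sees every past assignment, every third allocation can be deduced if the block size is known or inferred, so the sealed envelopes do not fully conceal

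*Protocol article*

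**What the plan says.** All references are to the protocol article.

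- **Design.** Trial Design describes a "single-center superiority trial with 3 parallel groups and a 1:1:1 allocation ratio". Participants confirms one site: "A single setting was selected for this study".
- **List.** The Randomization section plans a list of 85 assignments, drawn up by a statistician in permuted blocks. Its specification reads: "using SAS computer software (SAS Institute) and block sizes of 3, an allocation ratio of 1:1:1, and one strata". Only one block size is given.
- **Safeguards.** A research coordinator with no part in allocation transcribes the schedule into numbered opaque envelopes. The list is locked away and "will not made accessible to the interventionist involved in enrollment and treatment allocation".
- **Who does what.** That last quote places the interventionist in both enrolment and allocation. Training of Interventionist and Timing of Interventions adds: "One interventionist will deliver the hand massage and hand-holding interventions". Recruitment of Participants states: "The interventionist will then administer the assigned intervention (hand massage, hand-holding) without informing participants of their group assignment". Under Passive Control Group, the same person stays outside the room during the rest period. Data Collection masks this person to the patients' self-reports; nothing masks this person to allocation.
- **Claim.** Recruitment of Participants concludes that taking the next envelope in sequence hides the coming assignment from the interventionist and the participants.

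**The concern.** Opaque envelopes and a locked list stop someone from reading ahead. They do not stop someone from working out the next assignment from those already made. When the block size equals the number of arms, each arm appears exactly once per block, so two known assignments fix the third. With one centre and one stratum there is a single sequence to follow, and the person who follows it also helps to enrol.

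At stake is selection. Someone who can tell which arm comes next could, even without intending it, let that knowledge colour who is judged eligible or in what order patients are entered. The primary outcome is self-reported, and the Limitations section already concedes that the rest arm is unlikely to be blinded. Concealment before assignment is therefore one of the protections the trial most depends on.

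**Working it through.** **Inputs.** Block size 3, three arms at 1:1:1, one stratum and a list of 85 (Trial Design; Randomization); one centre (Trial Design; Participants); N = 79 (Sample Size and Sampling Procedure); 34 recruited and 24 randomised so far (Results). The article gives no figure for predictability, so there is none to reproduce. The 79 is taken as given, and block size does not affect it.

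**Assumption.** The observer knows all past assignments and the block size, and always guesses the arm with most places left in the block.

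**Step 1, one block.** The chance of a correct guess is 1/3 in the first place, 1/2 in the second and 1 in the third. The mean is (1/3 + 1/2 + 1)/3 = 11/18 = 61.1%, against 33.3% by chance.

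**Step 2, the planned trial.** 79 = 26 × 3 + 1.
- Known with certainty: 26 of 79 (32.9%).
- Narrowed to two arms: another 26.
- Expected correct guesses: 26 × 11/6 + 1/3 = 48.0, against 79/3 = 26.3 by chance.

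For the full list, 85 = 28 × 3 + 1, so 28 are certain.

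**Step 3, what remains.** The 24 already randomised make 24/3 = 8 complete blocks. Of the remaining 79 − 24 = 55 = 18 × 3 + 1, the current list makes 18 certain.

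**Step 4, alternatives.** Fixed sizes were enumerated exactly. Mixed sizes were simulated (300 trials of 79), with an observer who knows the possible sizes but not the size of each block, and who updates after every assignment.

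| Block sizes | Known with certainty | Expected correct guesses |
|---|---|---|
| 3 (plan) | 33.3% | 61.1% |
| 6 | 20.0% | 56.1% |
| 9 | 14.3% | 53.2% |
| 3, 6 mixed | about 9% | about 57% |
| 3, 6, 9 mixed | about 4% | about 55% |
| 6, 9 mixed | about 5% | about 54% |
| 6, 9, 12 mixed | about 2% | about 52% |

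Mixing 3, 6 and 9 leaves 0.036 × 79, or about 3, allocations certain instead of 26. The overall guess rate falls much less, so the gain lies in removing certainty.

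**Step 5, is there room to act on it?** Consent is taken before surgery (Table 1), but the remaining eligibility criteria are checked afterwards, just before randomisation. Ability to answer questions and self-report needs some judgement. Sampling is by convenience. Results shows that 10 of 34 recruited patients (29%) had not been randomised, with instability after surgery and cancelled or postponed operations given as reasons. The article does not split the 10 by reason.

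**The case against.** The strongest reply has four parts.

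1. **Foreknowledge is conditional.** A statistician makes the list, an uninvolved coordinator fills the envelopes, and nothing says that the interventionist is told the block size. This stands: the result holds only if the size is known or inferred. But nothing says that it is withheld, the article prints it while recruitment is under way, and a run in which each arm appears once in every three patients is easy to notice.
2. **Concealment is not lost for everyone.** This stands. The first place in each block remains a one-in-three guess and the second an even one. A reader might infer that the envelopes are defeated outright; the arithmetic supports that only for the third place.
3. **Discretion is narrow.** This largely stands. Chest-drain bleeding has a numeric threshold, and a line in the hand is an observable fact, so neither is a judgement item. Table 1 fixes randomisation to the evening of surgery. What remains is mainly the judgement of ability to self-report, and convenience sampling.
4. **Other safeguards soften any effect.** The interventionist is masked to self-reports, baseline data precede randomisation, and the primary metric is change from before each intervention. These reduce the scope for choosing patients on their pain score. They do not make the next assignment less predictable.

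A reader might also put a size on the bias, for instance by supposing that patients steered into predictable places differ by one NRS point and reading off a shift of about 0.3 point. The documents give no basis for that difference, and the calculation ignores both the change metric and the masking to self-reports.

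**Conclusion.** The point holds as a weakness in concealment. With fixed blocks of 3, the plan makes 26 of 79 allocations deducible with certainty and narrows another 26 to two arms, giving 61% expected correct guesses against 33% by chance. This rests on two conditions. The first is that the interventionist knows every past assignment, which follows from the role although the article does not say so in words. The second is that this person knows or infers the block size, which the article neither states nor rules out. Under these conditions, the claim in Recruitment of Participants that the next assignment is hidden does not hold for the third place in each block.

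Nothing in the documents shows that selection took place, and no size of bias can be derived from them. The sample size and the analysis are unaffected. The weakness merits correction during recruitment because analysis afterwards cannot restore concealment.

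**What to change.** 1. From the next complete block, the statistician regenerates the unused part of the list with randomly varying block sizes in multiples of 3, for example 3, 6 and 9. At the reported 24 randomised a block has just ended; the boundary should be taken from the count on the day of the change.
2. Keep the new sizes out of every document that the interventionist sees, including any published update before recruitment ends.
3. State that eligibility is recorded and final before the envelope is opened. The article already places baseline data before randomisation; the eligibility decision should be fixed in writing at the same point.
4. Keep all assignments already made, and report the predictability of the earlier blocks as a limitation.

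Having someone else enrol patients, or reveal the allocation once eligibility and baseline are locked, would protect more directly if staffing allows.

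**Cost.** One new list, refilled envelopes and a possible final imbalance of a few patients. A block of 9 holds three places per arm, so if it is cut short two arms can differ by at most 3, against at most 1 with blocks of 3. The required N does not change.

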### Recruitment of Participants

Patient recruitment will begin preoperatively when eligibility criteria such as age and language spoken will be verified (Table 1).

The remaining eligibility criteria (eg, blood loss, peripheral intravenous lines) will be evaluated post–cardiac surgery and ICU admission. After the collection of baseline data, patients meeting all the inclusion criteria will be randomly assigned to either hand massage, hand-holding, or standard care. As each participant enters the study, he or she receives the next envelope in the sequence, thereby concealing the interventionist’s and trial participants’ knowledge of the upcoming group assignment.

The interventionist will then administer the assigned intervention (hand massage, hand-holding) without informing participants of their group assignment until the end of data collection. Nurses and other ICU clinicians will also be masked to patients’ group assignment. The similarity of the hand massage and hand-holding therapy characteristics serves to mask study participants and clinicians with regard to the specific intervention received as observed in a feasibility and acceptability study where patients receiving hand-holding referred to the intervention as massage [42]. Conversely, patients in the rest group are less likely to be masked to the group assigned.

A modified Consolidated Standards of Reporting Trials flow diagram for individual RCTs of nonpharmacologic treatments will be used to document recruitment and retention of participants [43].

### Choice of Comparators

The majority of massage studies include standard care control groups to examine the absolute efficacy of massage in improving outcome variables. While this is important in attributing benefits to the massage therapy itself, studies that involve the administration of massage by a trained therapist, as recommended in Cochrane Systematic Reviews [44], should equally include a touch control group to verify if the additional manipulation included in massage is superior to touch only. Some studies suggest that touch, a free and easily administered intervention not requiring training, can have potential pain relief effects [45] and should, thus, be included as an active control group in future RCT designs to additionally examine the relative efficacy of massage. Furthermore, the touch control group can help mask patients with regard to the group assigned through its resemblance with actual massage, thereby controlling for placebo effects [44].

### Interventions

#### Training of Interventionist and Timing of Interventions

Eligible patients will be randomized in equal proportions between hand massage, hand-holding, and standard care. One interventionist will deliver the hand massage and hand-holding interventions, which will be standardized across participants. The interventionist is a registered nurse with no previous experience in massage therapy who will be trained by a professional massage therapist through an accredited workshop of 6 hours including practical exercises and verification of competency, as was done in the pilot RCT [30].

The first intervention (hand massage or hand-holding) will be delivered in the evening of the day of surgery and the remaining two interventions the day after when patients are still in the ICU. Overall, three interventions will be administered within 24 hours postoperatively over the course of two days.

#### Experimental Group

Patients assigned to the experimental group will receive a 20-minute hand massage by the interventionist in addition to the standard ICU care. Before administering the massage, a favorable environment will be created that promotes calmness such as dampening the light, reducing the alarm intensity, closing the curtains and door, and posting a “do not disturb” notice, and a comfortable positioning of the patient will be ensured [9,30,46]. After performing hand hygiene and explaining the procedure to the patient, the interventionist will hold each hand for 5-10 seconds and apply 5-10 mL of unscented hypoallergenic cream to both hands and wrists. The cream will be supplied by the interventionist and reserved for use within the research context only. The interventionist will then perform massage using moderate pressure and stroking and kneading techniques during 10 minutes on the palm and back of each hand as inspired by the procedure by Kolcaba et al [47] and developed with the support of an experienced massage therapist (Textbox 2).

**Table 1 table1:** Study timeline.

Procedures		Preop	POD^a^ 0 evening	POD 1 early evening	POD 1 late evening	POD 2
**Recruitment**						
	First eligibility screen	x				
	Informed consent	x				
	Second eligibility screen		x			
	Randomization		x			
**Interventions**						
	Hand massage		x	x	x	
	Hand-holding		x	x	x	
	Rest period		x	x	x	
	Standard care	x	x	x	x	x
**Data collection**						
	Demographics questionnaire	x	x			
	Pain intensity		x	x	x	
	Pain unpleasantness		x	x	x	
	Pain interference					x
	Pain location and quality		x	x	x	
	Anxiety		x	x	x	
	Muscle tension		x	x	x	
	Vital signs		x	x	x	

^a^POD: postoperative day.

#### Active Control Group

The active control group will receive hand-holding by the same interventionist in addition to standard ICU care. The same hand hygiene and environmental adjustments will be made as for those receiving massage. Patients will have their hands held for 5-10 seconds and unscented hypoallergenic cream applied to both hands. Then, the interventionist will hold each of the patients’ hand in her hand for ten minutes with occasional stroking for a total of 20 minutes.

#### Passive Control Group

The passive control group will receive the standard care administered in the ICU including a 20-minute rest period including the environmental adjustments of the experimental and active control groups. The interventionist will be outside of the patient room and have no contact with the patient throughout the 20 minutes. The standard care includes the pharmacological and nonpharmacological treatments (eg, repositioning) used to promote recovery and pain relief. In the study ICU, cardiac surgery patients are automatically prescribed a pain management protocol that includes the regular administration of morphine and breakthrough doses of analgesia as needed.

### Criteria for Modifying Interventions

The allocated interventions will be discontinued upon the participant’s withdrawal of consent or if skin irritation is suspected or patient comfort is disrupted due to the intervention itself, both of which will be reported as adverse events. Consenting participants will be retained in the trial whenever possible in spite of the discontinuation of the assigned intervention to allow remaining data collection and limit missing data.

### Concomitant Care

Concomitant interventions may be received by patients while participating in this trial. Consenting patients will be permitted to receive any of the pharmacological treatments prescribed by their treating physician and any of the nonpharmacological interventions offered in the ICU (eg, back rub), and such data will be recorded. It is not prohibited that patients participate concomitantly in other research studies unless it involves any form of complementary therapy.

### Outcomes

#### Primary Outcome

Pain intensity is the primary outcome and will be captured using the 0 to 10 NRS score. The analysis metric will be the change in pain intensity from baseline (preintervention) to immediately after each intervention and 30 minutes later.

Hand massage routine protocol.1. Hygiene: Wash hands with warm water.2. Hold/connect/breathe: Make initial contact with patient, embrace hand, take a deep breath, and place feet on floor.3. Apply cream to entire hand, dorsal and palmer aspects, including phalanges.4. Spread (5 times) dorsal aspect of hand, using thumbs like opening a book. Repeat 5 times on palmer aspect, using the other 4 fingers to grip and glide. Spread again 5 times dorsal aspect of hand and 5 times palmer aspect.5. Gently shake bottom hand; vibration will help the patient relax and let go of any tension.6. Rotate wrists 3 times in each direction. Hold wrist with one hand while the other holds the patient’s hand and facilitates the passive rotation.7. Stretch the carpal ridge 3 times along wrist crease.8. Caterpillar walk on the dorsal aspect of the hand, between the bones (ie, zoning).9. Pinch (dorsal/palmer) aspect of the hand in between the metacarpals.10. Gently pull the webs of fingers.11. Knead (rock and roll) by making a fist on the palmer aspect of patient’s hand, gently rotate using the knuckles to apply pressure 5 times.12. Caterpillar walk on all areas of the palm, working proximally (towards the body) (if patient is less comfortable with palm upwards continue with hand in a neutral position, palm down).13. Make small circles along the 5 zones of the palmer surface of the hand (proximal to distal).14. Targeting key reflex areas, PRESS AND RELEASE 2 times in each area:  a. Shoulder-neck ridge (base of fingers)  b. Solar plexus (center of palm, just below the knuckle), PRESS and SPREAD (diaphragm line—moving outwards in both directions) 5 times  c. Lateral aspect of palm  d. Medial aspect of palm  e. Pad of thumb14. Pinch lateral aspect of hand 3 times.15. Caterpillar walk on the medial border of thumb 3 times.16. Caterpillar walk on the fingers:  a. Caterpillar walk proximal making sure to cover all surface areas.  b. Rotate knuckles gently 3 times in each direction (proximal to distal).  c. Gently pull fingers.17. Finishing touches: SWEEP entire hand, HOLD, and switch to other side.18. Hygiene: Once both hands have been massaged, wash hands with cold water.

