A recent systematic review exploring the effectiveness of massage on postoperative outcomes among patients undergoing cardiac surgery [24] indicated that out of the 7 eligible studies (N=40-252/study), 6 reported that massage therapy ranging from 20 to 30 minutes in duration improved postoperative outcomes such as pain, anxiety, and muscle tension [9,10,25-28], while only one study reported no positive results [29]. The latter study evaluated the effectiveness of a 30-minute massage therapy involving each limb for 5 minutes followed by a 10-minute back massage while patients were lying on the left side. The positioning required for the back massage might have obscured or minimized the potential benefit of massage in relieving pain, anxiety, and muscle tension given that side-lying may exert traction on the sternotomy site, causing pain [3] and increasing muscle tension and possibly anxiety as turning on one side could be perceived as a painful procedure. Of note, only one of these studies was conducted in the ICU [25], and it lacked random assignment.

One pilot randomized controlled trial (RCT) conducted with 40 ICU patients post–cardiac surgery [30] showed promising pain relief and muscle relaxant effects of up to 3 15-minute hand massages, whereas the administration of a single massage therapy did not yield any significant decrease in pain intensity or muscle tension, suggesting that repeated administration of hand massage is necessary in this patient population.

Overall, there is a paucity of high-level evidence on which to base massage therapy decisions in the management of pain in post–cardiac surgery ICU patients. Extrapolations of evidence from other patient populations and clinical settings are flawed by the differing health status and symptom severity of this specific subgroup of ICU patients. Future rigorous RCTs conducted in the context of the ICU and with cardiac surgery adults in their immediate postoperative period are essential to make recommendations for the use of massage in clinical practice including the minimal effective dose, body area massaged, and techniques employed.

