### Data Collection

Sociodemographic (eg, age, gender) and medical-surgical data (eg, type of cardiac surgery, analgesia) will be collected using standardized data collection sheets. Prior to the delivery of each intervention (hand massage or hand-holding) and before the first data collection for the standard care group, patients will complete a self-administered data collection sheet with 5 short questions using the NRS for the self-report of pain intensity, pain unpleasantness, and anxiety, a body map for identifying the site of pain, and an open-ended question for a description of the quality of pain. The interventionist will be masked to patients’ self-reports, which will be accessed only at the end of data collection to verify for missing data. The form will be completed before, immediately after the intervention (hand massage or hand-holding), and 30 minutes later, for a total of 3 data collection points per intervention. Those assigned to standard care will complete the form at similar times. This bundle of assessments will be repeated for each of the 3 interventions. Muscle tension and vital signs will also be evaluated at the same assessment points.

Finally, pain interference will be evaluated using a structured interview using the BPI on the second postoperative day to examine any carry-over effects.

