### Data Analysis

The data will be entered in the SPSS software version 22.0 (IBM Corp), and a random subset of data will be used to identify missing or erroneous values. This study aims to use intention-to-treat analysis by including every participant who has been randomized, regardless of group assignment, study withdrawal, or protocol deviations.

Descriptive statistics will be calculated for sociodemographic and medical-surgical data and the baseline scores on all the outcome variables. Group differentiation in sociodemographic and medical-surgical characteristics for participant patients will be investigated using chi-square tests of independence for nominal level variables and one-way analyses of variance (ANOVA) for interval and ratio level variables. If group differences exist, the respective variable will be included as a covariate in the subsequent analyses. Frequencies and percentages of the location and descriptors of pain (ie, sensory dimension of pain) will be calculated for each group and assessment point and used to describe the pain characteristics of participants. Data on pain location and quality will be compared over time.

Repeated measures between ANOVA factors will be used to test for treatment (hand massage, hand-holding, rest), time (before, immediately after, and 30 minutes later), and interaction effect for pain intensity, pain unpleasantness, muscle tension, anxiety, and means of vital signs. This will be run for each intervention and each of these outcome variables. One ANOVA test will be performed for pain interference with the independent variable being group assignment (hand massage, hand-holding, standard care). The main comparison of interest is between the hand massage and standard care group and the difference in means pre- and immediately posttreatment.

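### The main comparison is a within-session change, whereas the aim and sample size concern the pain score after a course of three massages; relief persisting to the third pre-score would be subtracted

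*Protocol article*

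**What the plan says.** All references are to the protocol article.

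- **Primary Outcome** defines the metric: "The analysis metric will be the change in pain intensity from baseline (preintervention) to immediately after each intervention and 30 minutes later".
- **Data Collection** shows that a pre-score exists at every session, since the same three readings are taken around each one: "This bundle of assessments will be repeated for each of the 3 interventions".
- **Data Analysis** gives the ANOVA's time factor as "time (before, immediately after, and 30 minutes later), and interaction effect for pain intensity" and adds "This will be run for each intervention and each of these outcome variables". It then singles out one contrast: "The main comparison of interest is between the hand massage and standard care group and the difference in means pre- and immediately posttreatment".
- **Recruitment of Participants** places allocation before the first session: "After the collection of baseline data, patients meeting all the inclusion criteria will be randomly assigned". Table 1 puts randomisation and session 1 on the evening of surgery, and sessions 2 and 3 on the next day.
- **Aim** is to compare the effect of three 20-minute massages on pain intensity.
- **Sample Size and Sampling Procedure** powers a 1.5-point difference in pain scores (SD 2.0) between massage and standard care, immediately after the third massage.
- **Background** reports that a single massage in the pilot gave no significant decrease, "suggesting that repeated administration of hand massage is necessary in this patient population".

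**The concern.** On its own, the word baseline in Primary Outcome could mean one score taken at the start of the trial. The other two sections point to a session-specific reading: a form before each session, a model for each session whose first time level is before, and a pre-to-post contrast. No section carries the session-1 score forward to session 3.

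At session 1 this does no harm. At session 3 the pre-score follows two allocated interventions, so it is itself a possible outcome of treatment. The main contrast then measures what the third session adds to whatever the first two left behind. That is a different quantity from the effect of the three-massage course in the Aim and from the score difference in the sample size section. If massage has a lasting effect, the named main comparison could miss a benefit that the trial was sized to find.

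**Working it through.** **1. The plan's own figure.** The inputs from the sample size section are a difference of 1.5, SD 2.0, two-sided alpha 0.05, power 0.80, three equal arms and three measurements. Two inputs are not stated and are assumed here: hand-holding lies midway (means 0, 0.75, 1.5) and the correlation between measurements is 0.5.

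- Effect size f = SD of the means / 2.0 = 0.612 / 2.0 = 0.306.
- Noncentrality = f² × N × m / (1 + (m − 1) × rho) = 0.09375 × 72 × 3 / 2 = 10.125, with df 2 and 69.
- Power = 0.802, so the stated minimum of 72 is reproduced.

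This calculation is for a between-group difference in score level averaged over the measurements. It is not for a pre-to-post change.

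**2. The named main comparison at session 3.** Let the true massage versus standard care difference immediately after session 3 be 1.5, and let a share s of it already be present at the session-3 pre-score. The documents give no value for s, so a range is shown.

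- Expected change contrast = 1.5 × (1 − s).
- SD of change = 2.0 × √(2 × (1 − rho)) = 2.0 at rho 0.5.
- Standard error with 24 per arm = 2.0 × √(2/24) = 0.577.
- Power is from the noncentral t with df = 72 − 3 = 69.

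**3. The treatment main effect in the same session-3 ANOVA.** This averages the three readings, so it does not subtract the pre-score. Assume that the 1.5 also holds at 30 minutes.

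- Expected contrast = (1.5s + 1.5 + 1.5) / 3.
- SD of the mean of three readings = 2.0 × √((1 + 2 × 0.5) / 3) = 1.633.

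| Share present before session 3 | Pre-to-post contrast | Power | Main-effect contrast | Power |
|---|---|---|---|---|
| 0% | 1.5 | 73% | 1.0 | 55% |
| 25% | 1.125 | 48% | 1.125 | 65% |
| 50% | 0.75 | 25% | 1.25 | 74% |
| 75% | 0.375 | 10% | 1.375 | 82% |
| 100% | 0 | 5% | 1.5 | 88% |

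At 50% persistence the power of the pre-to-post contrast is 19% at rho 0.3 and 38% at rho 0.7, so the fall does not hinge on rho 0.5.

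**4. Anchoring to the score before session 1.** The expected contrast stays at 1.5 whatever s is.

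- Simple change from the session-1 score, rho 0.5: SD 2.0, power 73%.
- ANCOVA on the session-1 score: SD = 2.0 × √(1 − rho²), df 68. At rho 0.1, 0.3 and 0.5 the SD is 1.990, 1.908 and 1.732, and power is 73%, 77% and 84%.

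At rho 0.5, the rise from 73% to 84% therefore comes from covariate adjustment, not from the choice of baseline. What the choice of baseline secures is that the contrast does not shrink with carry-over.

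**The case against.** The strongest counter-argument is that within-session change answers a legitimate question: how much one session relieves pain. The secondary outcomes are also framed in relation to each intervention, and the mechanism in the Theoretical Framework says nothing about relief lasting between sessions. The pilot result fits a larger response to each session with repetition as well as it fits relief that persists. This stands. Only relief that lasts to the next pre-score is subtracted, and if none lasts, nothing is lost.

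A reader might infer that the planned analysis as a whole removes the cumulative effect. The documents do not support that. Data Analysis also plans a treatment main effect, whose power rises with persistence (55% to 88% above), and the sample size is reproduced from a between-group test of that kind. The loss is confined to the pre-to-immediately-post contrast. That is, however, the contrast the protocol names as the main one.

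A reader might also infer that a pre-randomisation pain score is certainly in hand. Recruitment of Participants says that baseline data precede allocation, and Data Analysis refers to baseline scores on all outcomes, so this is likely. But no section states that the first pain form is completed before allocation, and Table 1 puts both in the same column. What is certain is a score taken before the first session.

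Leaving the matter to an analysis plan is not a full answer, because the protocol itself fixes the metric, the model and the main comparison.

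**Conclusion.** The mismatch is established from the text: the aim and the sample size concern pain after three massages, and the main comparison concerns change within one session. This holds whatever the carry-over.

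The numerical harm is conditional. It runs from none at zero persistence to a power of about 10% at 75% persistence, under the assumed 1.5-point true effect, SD 2.0, correlation 0.5 and 24 per arm. The 73% at zero persistence is below the planned 80% because a two-arm contrast is being tested instead of the three-arm averaged test; that gap is not caused by the choice of baseline. It would be too strong to call the metric biased toward no effect without qualification, since it is a sound measure of a session's acute effect and the amount of persistence is unknown.

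This should be fixed, but it does not invalidate the trial.

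**What to change.** In Primary Outcome and Data Analysis, name as the main comparison the massage versus standard care difference in pain intensity immediately after the third session, adjusted by ANCOVA for the score taken before the first session. State that this score is recorded before allocation, after confirming that this was so for the patients already randomised. Keep the within-session pre-to-post change as a secondary measure of each session's acute effect.

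The cost is rewording in two sections, with no new data, because all the scores are already collected. One small downside is that a score taken a day earlier may correlate less with the outcome than the same session's pre-score. Even at a correlation of 0.1, ANCOVA power is about 73%, equal to that of the present contrast with no carry-over at correlation 0.5.
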